#### Secondary outcomes

2.8.2

1.Seattle Angina Questionnaire (SAQ) scores:

The SAQ-SS and individual SAQ domain scores will be assessed at baseline, week 4, and week 8 to evaluate continuous changes in angina-related symptoms and health status.
2.Angina attack frequency:Angina episodes will be continuously recorded and evaluated using an angina diary from baseline through the end of the 8-week follow-up period. The diary will document the onset time, end time, duration of each episode, pain intensity measured by the visual analogue scale (VAS), accompanying symptoms, medication use, nitroglycerin dosage, and symptom relief.
3.EuroQol five-dimension five-level questionnaire (EQ-5D-5L):The EQ-5D-5L will be assessed at baseline, week 4, and week 8. This instrument includes five dimensions: mobility, self-care, usual activities, pain/discomfort, and anxiety/depression, each rated on a five-level scale (29). In addition, the EQ visual analogue scale (EQ-VAS) will be recorded to reflect the participant's self-rated health status on the day of assessment. The EQ-5D-5L will be used to evaluate the impact of acupuncture on overall health status and quality of life.
4.Traditional Chinese medicine (TCM) syndrome score:The TCM syndrome score will be assessed at baseline, week 4, and week 8. The scoring system includes the following major symptoms: chest pain and chest tightness, each scored as 0, 2, 4, or 6 points; and the following minor symptoms: palpitations, shortness of breath, fatigue, spontaneous sweating, and dark complexion, each scored as 0, 1, 2, or 3 points. Tongue manifestation, tongue coating, and pulse condition will each be scored as 0 or 1 point. A higher total score indicates more severe manifestations of qi deficiency and blood stasis syndrome. The total TCM syndrome score and its change from baseline will be compared between the two groups to evaluate the effect of acupuncture on qi deficiency and blood stasis syndrome.
5.Endothelial function and inflammation-related biomarkers:Blood samples will be collected at baseline and week 4 for measurement of nitric oxide (NO), endothelin-1 (ET-1), and high-sensitivity C-reactive protein (hs-CRP). These markers will be used to reflect changes in endothelial vasomotor function and inflammatory status and to explore the potential biological effects of acupuncture in CMVD (30, 31). These biomarkers are intended to explore short-term treatment-related changes in endothelial function and inflammatory status during the intervention period.

#### Additional outcomes

2.8.3

Additional outcomes in this study will include baseline expectancy assessment, credibility assessment of acupuncture therapy, the Clinical Global Impression–Improvement scale (CGI-I), and participant blinding assessment.

Baseline expectancy will be assessed before the first treatment session. Credibility of acupuncture will be evaluated at baseline and again at week 4 (32). The CGI-I will be assessed at week 4 and at the end of follow-up to capture participants' global perception of change relative to baseline (33). Participant blinding assessment will be completed within 5 min after the final treatment session at week 4. Participants will be asked to guess whether they received true acupuncture, sham acupuncture, or were unsure. The success of blinding will be evaluated by comparing the distribution of allocation guesses between groups (34).

Because objective evidence of myocardial ischemia is required for inclusion, this study focuses on INOCA-related CMVD rather than broader ANOCA or asymptomatic coronary microvascular dysfunction. Accordingly, the symptom- and quality-of-life-related outcomes, including SAQ scores, angina attack frequency, EQ-5D-5L, and CGI-I, will be evaluated in a symptomatic INOCA-related CMVD population.

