#### Sham acupuncture group

2.7.2

Participants in the sham acupuncture group will receive sham acupuncture in addition to conventional drug therapy, using the same acupoints and treatment schedule as the acupuncture group. After routine disinfection and placement of adhesive pads, a blunt-tipped sham needle (0.30 mm × 25 mm; Huatuo, Suzhou, China) will be applied so that it passes through the pad and touches the skin surface without penetrating the skin or subcutaneous tissue, and deqi will not be sought. The sham procedure will be matched with true acupuncture in terms of acupoint location, participant position, treatment environment, treatment frequency, session duration, and overall treatment course. Contact pressure will be kept light and as consistent as possible across sessions. The needle-withdrawal procedure will be identical to that in the acupuncture group.

All procedures will be performed by licensed traditional Chinese medicine practitioners certified by the National Health Commission of the People's Republic of China, each with at least 2 years of clinical experience in acupuncture.

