#### Primary outcome

2.8.1

The primary outcome is the overall clinical response rate at week 4, defined as the proportion of participants who achieve an increase of at least 5 points in the Seattle Angina Questionnaire summary score (SAQ-SS) from baseline. The Seattle Angina Questionnaire (SAQ) is a disease-specific 19-item instrument comprising five domains—physical limitation, angina stability, angina frequency, treatment satisfaction, and quality of life—with each domain scored from 0 to 100; higher scores indicate better angina-related health status (26). The SAQ-SS is calculated as the mean of the physical limitation, angina frequency, and quality-of-life domain scores (19). Consistent with previous studies, an increase of 20 points or more will be considered a large improvement, an increase of 5–19 points a clinically meaningful improvement, and an increase of less than 5 points, no change, or deterioration as no response (27, 28). The responder rate will be calculated as the number of participants with an SAQ-SS increase of at least 5 points divided by the total number of participants.

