## Discussion

3

CMVD remains a therapeutic challenge even after diagnostic recognition, and the gap between pathophysiological classification and meaningful symptom improvement is still substantial (38, 39). This exploratory sham-controlled trial therefore focuses on a clinically relevant question: whether acupuncture can provide incremental benefit beyond stable conventional therapy in patients with persistent symptoms. This question is important because symptom burden, functional limitation, and health status remain central concerns in CMVD care, and structured patient-reported outcome measures are increasingly emphasised in mechanism-based management pathways (21, 30).

A further strength of the protocol is its multidimensional outcome framework. In CMVD, symptom relief alone may not fully reflect treatment response. Combining SAQ-based health-status assessment with endothelial and inflammation-related biomarkers may improve interpretation of early-phase trial findings and help generate hypotheses regarding potential biological pathways (17, 31).

The choice of sham acupuncture as the control is methodologically important in this trial. Because key outcomes such as SAQ-based health status, angina frequency, and CGI-I are vulnerable to expectation and contextual effects, sham acupuncture may better control for non-specific effects related to practitioner attention, treatment ritual, and patient-provider interaction than usual care alone. In this study, the sham group receives the same acupoints and treatment schedule as the acupuncture group, but with non-penetrating blunt-tipped needles, in order to strengthen participant blinding and improve internal validity. However, sham acupuncture may not be completely physiologically inert, which should be considered when interpreting between-group differences.

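### With 24 to 30 guesses per arm, a lack of difference in allocation guesses after the last session should not be read as successful blinding, and a difference may partly reflect felt benefit

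*Protocol article*

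**What the plan says.** Section 2.8.3 (Additional outcomes) of the Protocol article sets one allocation guess: "Participant blinding assessment will be completed within 5 min after the final treatment session at week 4". Table 1 agrees, with blinding assessment marked in the 4-week column only. There are three answer options: "Participants will be asked to guess whether they received true acupuncture, sham acupuncture, or were unsure". The judgement follows: "The success of blinding will be evaluated by comparing the distribution of allocation guesses between groups". A literature reference is attached to that sentence, but no index, confidence interval or margin is named.

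The primary endpoint falls at the same time point: "The primary outcome is the overall clinical response rate at week 4" (2.8.1). It is a responder rate on the SAQ summary score, which participants report themselves. The Discussion says that SAQ-based health status, angina frequency and CGI-I "are vulnerable to expectation and contextual effects". The arms also feel different by design. Deqi is elicited in the acupuncture arm (2.7.1), whereas the sham needle "touches the skin surface without penetrating the skin or subcutaneous tissue, and deqi will not be sought" (2.7.2).

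Two related measures exist. Expectancy is taken before the first session, and "Credibility of acupuncture will be evaluated at baseline and again at week 4". Neither asks for an allocation guess.

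**The concern.** The trial relies on the sham to protect self-reported outcomes, so readers will look to the blinding assessment when they interpret any difference. As described, it has two weaknesses.

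- **No difference in guesses.** With 24 to 30 guesses per arm, the comparison would often miss a real gap. Without an estimate and interval, a null result could be taken as support for masking that it does not give.
- **A difference in guesses.** After four weeks of treatment, participants know whether their angina has eased. If acupuncture works, guesses can diverge even under perfect masking. A single guess at the end cannot separate recognition of the procedure from inference based on benefit.

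A smaller matter is order. The guess is due within 5 minutes of the last session. Any week-4 SAQ completed later would follow a question that draws attention to allocation. The article does not say which comes first.

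**Working it through.** **Numbers per arm.** Section 2.10 starts from 25 per group and allows for about 20% dropout: 25 × 1.20 = 30 per group, 60 in total, which reproduces the stated figure. If 20% of 30 drop out, 30 × 0.80 = 24 remain. The range used is therefore 24 to 30 guesses per arm. The two-sided 5% level is from section 2.11. That section names chi-square or Fisher's exact test for categorical secondary outcomes; applying them to the guesses is an assumption.

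**Chance of seeing a real gap.** Assume that 70% of the acupuncture arm and 50% of the sham arm guess true acupuncture. By the unpooled normal approximation, SE = √[(0.70×0.30 + 0.50×0.50)/n] = √(0.46/n) and power = Φ(0.20/SE − 1.96).

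- n = 30: SE = 0.124, 0.20/SE = 1.62, power about 37%.
- n = 24: SE = 0.138, 0.20/SE = 1.44, power about 30%.

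Other methods and assumed rates give similar or lower power:

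| Assumed guesses | Test | n = 24 | n = 30 |
|---|---|---|---|
| 70% vs 50% true | chi-square | 29% | 35% |
| 70% vs 50% true | Fisher's exact | 21% | 26% |
| 60% vs 40% true | chi-square | 28% | 34% |
| true/sham/unsure 50/20/30 vs 30/40/30 | 2×3 chi-square | 30% | 37% |
| 70% vs 40% true | chi-square | 55% | 65% |

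For 80% power by chi-square, the gap would have to be about 40 points (n = 24) or 36 points (n = 30), centred on 50%.

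**What a null result leaves open.** With 50% guessing true in both arms, the 95% interval for the difference has half-width 1.96 × √(0.50/n), which is 28 points at n = 24 and 25 points at n = 30. To show similarity within ±20 points (an illustrative margin; two one-sided 5% tests, 80% power, no true difference) would need 0.50 × [(1.645 + 1.282)/0.20]² ≈ 107.1, so 108 per group.

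**Felt benefit alone.** Assume that guesses depend only on response: responders guess true 75% of the time and non-responders 35%, with response rates of 70% and 50%.

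- Acupuncture: 0.70×0.75 + 0.30×0.35 = 0.63.
- Sham: 0.50×0.75 + 0.50×0.35 = 0.55.

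This is an 8-point gap with no procedural unblinding. With response of 60% vs 40% and guess rates of 80%/30%, the gap is 10 points (60% vs 50%). With response of 70% vs 40% and guess rates of 80%/20%, it is 18 points (62% vs 44%); with 90%/10% it is 24 points (66% vs 42%).

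**Precision of a per-arm index.** The Bang index in an arm is the proportion guessing correctly minus the proportion guessing incorrectly, with unsure counted as zero. At an index of 0, its 95% half-width is 1.96 × √[(1 − unsure)/n].

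| Unsure | n = 24 | n = 25 | n = 30 |
|---|---|---|---|
| 0% | 0.40 | 0.39 | 0.36 |
| 30% | 0.33 | 0.33 | 0.30 |

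The half-width is thus about 0.30 to 0.39 at 25 to 30 per arm, and up to 0.40 at 24.

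**The case against.** The strongest objection is that the article fixes little here. It states no test, P value or decision rule for blinding. Its general test wording covers categorical secondary outcomes, while blinding is an additional outcome. The cited reference, or an analysis plan that is not shown, may supply an index and interval, and the three-option question already collects the data for one. Comparing distributions is not wrong in itself, because intact masking predicts equal distributions. All of this stands. A reader might infer that a non-significant result will be declared success; the text does not say so. What remains is a judgement of success tied to a between-group comparison, with nothing stated that would show how little a null result means.

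The guess and response rates above are assumed. In the mildest example, benefit alone moves guesses by 8 points, which a test with 30 per arm would flag only about 9% of the time. The larger gaps need stronger assumptions.

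A reader might also conclude that the assessment is uninformative in both directions, or that an early guess should replace the late one. Neither follows. A large imbalance would still show, and credibility, expectancy and the masking procedures in section 2.6 add context. An early guess does not describe masking at week 4, when the primary outcome is taken, and asking it may prompt participants to think about allocation.

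Finally, Table 1 puts the SAQ and the guess in the same 4-week column, but nothing says that they share a visit or that the guess comes first. The order may be set in the full protocol or case report form.

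**Conclusion.** The point holds as a minor one about interpretation. Under assumed guess rates of 70% and 50%, a real 20-point gap would be detected about 30% to 37% of the time at 24 to 30 per arm, and less often with Fisher's exact test. A lack of difference should therefore not be read as successful blinding. A difference may partly reflect felt benefit; depending on the assumptions, benefit alone gives about 8 to 24 points. These sizes rest on assumed rates, because the article gives none. That a null result at this size is weak evidence does not depend on the exact rates, unless the true gap is nearer 35 to 40 points. The primary test is not affected; what is affected is how far the self-reported results can be attributed to needling rather than expectation.

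**What to change.** - Report the Bang index for each arm with its 95% confidence interval from the three-option guess, and do not declare blinding successful from a null between-group comparison. The data are already collected, so this costs only wording. The interval will be wide, but the imprecision is then visible.
- State that the week-4 SAQ is completed before the guess is asked. This costs one line in the visit procedure, and some care with scheduling because the guess is due within 5 minutes of the last session.
- Describe the end-of-treatment guess as a mixture of unblinding and perceived benefit when reporting it.
- Optionally, ask the same question after an early session as a supplement to the week-4 guess. It costs one question at an existing session and may prompt participants to think about allocation. It cannot be recovered later, so it has to be decided before treatment starts.

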### Safety evaluation

2.9

An adverse event will be defined as any unfavorable medical occurrence during the trial, regardless of its causal relationship with the intervention. A serious adverse event will be defined as an event resulting in death, life-threatening condition, hospitalization or prolongation of hospitalization, persistent or significant disability, or any other medically important event. The severity of adverse events will be graded as mild, moderate, or severe, with reference to CTCAE version 5.0 where applicable. Cardiovascular adverse events, including newly developed arrhythmia, heart failure, and acute myocardial infarction, as well as acupuncture-related adverse events such as syncope, intolerable pain, local hematoma, and infection, will be recorded in detail. The type, onset and resolution time, severity, management, and outcome of each adverse event will be documented in the case report form.

Preventive measures for acupuncture-related adverse events will include treatment by licensed practitioners, use of sterile disposable needles, routine skin disinfection, appropriate participant positioning, and close observation during and after treatment. Before each session, participants will be advised to have an appropriate light meal, obtain adequate rest, and avoid fasting, fatigue, or excessive emotional stress. During treatment, practitioners will closely observe the participant's facial expression, sweating, dizziness, palpitations, nausea, and other symptoms. Local hematoma will be managed by compression and observation; vasovagal syncope will be managed by immediate cessation of needling, needle removal, appropriate positioning, vital-sign monitoring, and supportive care; suspected infection will be evaluated and treated promptly; and intolerable pain will lead to cessation or adjustment of the procedure.

Any serious adverse event will be reported immediately to the principal investigator and to the ethics committee within 24 h or according to institutional requirements. Whether the participant continues, temporarily suspends, or withdraws from the trial will be determined by the investigator according to clinical judgment and participant safety. The incidence of adverse events in each group will be summarized after completion of the 8-week study period.

### Sample size

2.10

Given the pilot nature of this trial and the limited high-quality randomized evidence on acupuncture specifically for INOCA-related CMVD, a reliable effect size for a formal confirmatory sample size calculation is not available. Previous acupuncture studies in angina-related conditions support the clinical relevance of SAQ-based outcomes, but their populations, diagnostic criteria, and interventions are not sufficiently comparable to provide a directly transferable effect-size estimate for this trial. Therefore, the sample size was chosen to support feasibility assessment and to obtain preliminary estimates of variability and effect size, especially for SAQ-SS changes and the week 4 responder rate. On the basis of commonly cited recommendations for pilot studies, 25 participants per group was considered appropriate to assess feasibility, estimate variance, and obtain preliminary effect-size information (35, 36). Allowing for an anticipated dropout rate of approximately 20%, 60 participants (30 per group) will be recruited (37). The results of this pilot trial will be used to inform the design and sample-size estimation of future multicenter confirmatory randomized trials.

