### Study design

2.1

This is a prospective, single-center, parallel-group, randomized, sham-controlled exploratory trial. The protocol was prepared in accordance with the SPIRIT 2025 statement (22), with the corresponding checklist provided in Supplementary Table S1, and the acupuncture intervention is reported with reference to the revised STRICTA recommendations (23), as detailed in Supplementary Table S2. Sixty eligible participants will be randomly assigned in a 1:1 ratio to the acupuncture group or the sham acupuncture group.

Each participant will be followed for 8 weeks, including baseline assessment within 24 h after enrollment, 4 weeks of treatment, and 4 weeks of post-treatment follow-up. The primary objective is to evaluate the efficacy and safety of acupuncture as an adjunct to conventional therapy for INOCA-related CMVD and to explore its potential effects on angina-related health status, quality of life, endothelial function, and inflammation-related biomarkers.

This study protocol is version 1.0. It has been approved by the Ethics Committee of Guang'anmen Hospital, China Academy of Chinese Medical Sciences, and was registered with the International Traditional Medicine Clinical Trial Registry on March 13, 2026 (registration number: ITMCTR2026000515). The trial will be conducted in accordance with the Declaration of Helsinki. Eligible participants will be enrolled voluntarily and will provide written informed consent before any study-specific procedure. The study flowchart and the schedule of enrollment, interventions, and assessments are shown in Figure 1 and Table 1.

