### Statistical analysis

2.11

All analyses will be performed using SPSS version 27.0, and figures will be generated using GraphPad Prism version 10. The primary analysis will follow the intention-to-treat principle, with per-protocol analysis conducted as sensitivity analysis. Safety analysis will include all participants who receive at least one treatment session. Baseline characteristics will be summarized by group using appropriate descriptive statistics. Continuous variables will be presented as mean ± standard deviation or median with interquartile range, as appropriate, and categorical variables as frequencies and percentages. Baseline comparability between groups will be assessed descriptively and, where appropriate, using *t*-test or Mann–Whitney *U*-test for continuous variables and chi-square test or Fisher's exact test for categorical variables. The primary outcome, overall clinical response rate at week 4, will be compared between groups using logistic regression, with results reported as odds ratios and 95% confidence intervals. Repeated continuous secondary outcomes will be analysed using mixed-effects models, including group, time, and group-by-time interaction. Categorical secondary outcomes will be analysed using chi-square test or Fisher's exact test, as appropriate. Missing primary outcome data will be handled by multiple imputation when the proportion of missing data is non-negligible and the missing-at-random assumption is considered reasonable. Complete-case analysis and per-protocol analysis will be conducted as sensitivity analyses to evaluate the robustness of the primary findings. As this is an exploratory pilot trial, secondary outcome analyses will be considered exploratory. All tests will be two-sided, with *P* < 0.05 considered statistically significant.

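### Thirty per group with about 20% dropout leaves about 24 per group, not the 25 that section 2.10 takes as its target

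*Protocol article*

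**What the plan says.** The numerical basis for the sample size is in section 2.10 (Sample size) of the protocol article, in two adjacent sentences. The first sets the target, citing pilot-study recommendations: "25 participants per group was considered appropriate to assess feasibility, estimate variance, and obtain preliminary effect-size information". The second turns that target into a recruitment figure: "Allowing for an anticipated dropout rate of approximately 20%, 60 participants (30 per group) will be recruited". Section 2.1 (Study design) repeats the total and the allocation: "Sixty eligible participants will be randomly assigned in a 1:1 ratio to the acupuncture group or the sham acupuncture group".

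The same section explains why there is no power calculation: "a reliable effect size for a formal confirmatory sample size calculation is not available". The article does not say how the dropout allowance was applied, and no other section gives a different target, dropout rate or recruitment number.

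**The concern.** A dropout allowance is meant to leave the target number after losses. The target is 25 per group, the planned loss is about 20% and the recruited number is 30 per group, so 20% off 30 should give back at least 25. It does not.

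What is at stake is whether the stated justification is consistent with itself. With no effect size, power or precision target behind the sample size, the figure of 25 and the dropout allowance are the whole numerical argument for 60. The trial is also meant to inform the sample size of a later confirmatory trial. If the allowance was multiplied on and the same method were carried forward, that trial would fall short of its own target by the same proportion.

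**Working it through.** **Inputs, all from section 2.10:** target n = 25 per group; anticipated dropout d = 0.20 (given as approximate); recruited N = 30 per group, 60 in total. The 1:1 allocation is in section 2.1.

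**Step 1. Reproduce the stated figure.** Multiplying the target by one plus the dropout rate gives n × (1 + d) = 25 × 1.20 = 30 per group, 60 in total. This matches exactly. The article gives no formula, so the method is inferred from the match.

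**Step 2. Check it backwards.** Expected number left after dropout: N × (1 − d) = 30 × 0.80 = 24 per group, 48 in total. That is 1 per group and 2 in total below 25 and 50. This step does not depend on how 30 was obtained.

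**Step 3. Inflation that would meet the target.** n / (1 − d) = 25 / 0.80 = 31.25, rounded up to 32 per group, 64 in total. Check: 32 × 0.80 = 25.6.

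**Step 4. Dropout rate at which 30 is enough.** 1 − 25/30 = 0.167, so 30 per group leaves 25 only if dropout is at most 16.7%.

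**Step 5. Allow for the word approximately.** Expected number left from 30 per group:

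| Dropout | Left per group |
|---|---|
| 15% | 25.5 |
| 16.7% | 25.0 |
| 18% | 24.6 |
| 20% | 24.0 |
| 22% | 23.4 |
| 25% | 22.5 |

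Within two percentage points of 20% on either side, the target is missed throughout.

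**Step 6. Size of the consequence.** For a given variance, the standard error of a group mean or proportion, or of a difference between two equal groups, varies as 1/√n. Going from 25 to 24 per group multiplies it by √(25/24) = 1.021, an increase of about 2%.

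**Step 7. If the method were reused.** Multiplying by 1.20 and then losing 20% leaves 1.20 × 0.80 = 0.96 of the target, a 4% shortfall at any sample size.

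**The case against.** The best defence is that nothing in this trial depends on 25. The article says only that this number was considered appropriate, on the strength of general recommendations for pilot studies. It sets no power, precision target or success criterion that 24 would miss. This stands. A reader might infer that the protocol requires 25 per group, that the trial is underpowered as a result, or that 64 must be recruited. The document supports none of these, because there is no power claim to undermine.

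A second defence is that the dropout rate is only approximate and 60 is a round number, so a rate near 17% may have been meant. The approximate wording makes this arguable, and the multiplication remains an inference. But the planning value in print is 20%, and if about 17% was intended the sentence should say so.

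A third defence is that section 2.11 (Statistical analysis) plans an intention-to-treat primary analysis, with multiple imputation of missing primary outcomes when missingness is non-negligible and missing-at-random is reasonable. The number with observed outcomes then matters most for the complete-case and per-protocol sensitivity analyses. This softens the point but does not remove it: imputation does not recover the lost observations, and by adding a dropout allowance the protocol itself treats 25 as a number left after losses.

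Two further arguments might be used to make the point look larger, and neither holds. A reader might calculate the chance that both groups keep at least 25 and find it low. The protocol gives an expected-value allowance and promises no such thing, and even 32 per group would meet that criterion only about half the time. A reader might also cite the wide confidence interval for the responder difference. That width belongs to any pilot of this size and barely changes between 24 and 25 per group, and the article gives no responder rates from which to calculate it.

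**Conclusion.** The inconsistency is real and can be checked from section 2.10 alone. Thirty per group with the stated 20% dropout leaves about 24 per group, not 25, and 30 is enough only if dropout is at most 16.7%. That the allowance was multiplied on rather than divided out is a likely explanation, not a stated fact; the mismatch holds either way.

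The effect on the trial is minor: an expected one participant per group, two overall, and a standard error about 2% larger. This takes 20% at face value and assumes equal groups of 30 with the same loss in each. It calls for a correction to the text. It does not call for a change to recruitment, design or analysis, and no conclusion that the pilot is meant to support turns on it.

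**What to change.** Keep 60 participants and reword the dropout sentence in section 2.10 in one of two ways:

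- 60 participants (30 per group) will be recruited; at a dropout of about 20%, about 24 per group are expected to be evaluable; or
- 60 participants (30 per group) will be recruited, which gives 25 evaluable per group if dropout does not exceed about 17%.

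The sponsor should choose the version that matches the dropout rate it actually expects. The cost is one sentence, with no extra patients and no change to randomisation or analysis. When the confirmatory trial is sized, the allowance should be divided out, n/(1 − d), so that the 4% shortfall is not carried forward.
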